## Abstract

**Background and aim:**

Head and neck cancer patients are vulnerable to various psychological complications due to the effects of both cancer itself and cancer treatment on patients’ appearance and physical well-being. Nevertheless, few data have been obtained on effective psychosocial interventions that could protect this group of cancer patients’ psychological well-being. Therefore, this three-armed, parallel-group, double-blind, randomized control trial (RCT) aims to evaluate and compare the effects of acceptance and commitment therapy (ACT) and mindfulness-based stress reduction (MBSR) on positive psychology (such as posttraumatic growth [PTG], hope, and optimism), quality of life (QoL), and psychological complications (depression, anxiety, and experiential avoidance) among newly diagnosed head and neck cancer patients.

**Methods and analysis:**

This RCT will target newly diagnosed head and neck cancer patients who have been treated only with surgery or who have not yet received any treatment. In total, 120 patients who meet all of the study’s inclusion criteria and none of its exclusion criteria will be randomly assigned into three groups—an ACT group, an MBSR group, and a treatment-as-usual control group—at a 1:1:1 allocation ratio. Participants in the two intervention groups (the ACT and MBSR groups) will undergo an eight-week group intervention program. During this program, each intervention will comprise eight modules based on ACT and MBSR, respectively. Outcome assessments will be performed across a three-point timeline, including before the intervention (t_0_), immediately after the psychosocial intervention at eight weeks (t_1_), and six months after the intervention (t_2_). The primary outcome that will be assessed during this RCT is PTG. Meanwhile, the secondary outcomes that will be evaluated in this study are such as QoL, hope, optimism, depression, anxiety, and experiential avoidance.

**Trial registration number:**

NCT04800419 (ClinicalTrials.gov). Registered on March 16, 2021.

## Introduction

### Head and neck cancer and its associated psychological issues

Head and neck cancer is a group of biologically similar cancers that affect the oral cavity, lips, nasal cavity, paranasal sinuses, pharynx, and larynx. It affects 550,000 people worldwide annually, leading to 300,000 deaths each year [1]. In Malaysia, 9,419 head and neck cancer cases were reported between 2007 and 2011, accounting for 9.1% of all cancer diagnoses [2]. Therefore, head and neck cancer is the country’s fourth-most-prevalent cancer [2]. Head and neck cancer leads to high incidence of various psychosocial issues among cancer survivors, such as depression, suicide, interpersonal relationship conflict, facial disfigurement, damage to self-image, social isolation, and continued substance dependence and abuse [3]. These psychosocial issues may lead to negative consequences in head and neck cancer survivors. For example facial disfigurement can increase depression and reduce quality of life (QoL) among head and neck cancer patients [4].

Some studies have found that head and neck cancer is associated with the highest documented rates of depression and anxiety compared with other cancer types [5]. Depression and anxiety could reduce head and neck cancer patients’ QoL [6]. A 2003 article by Spiegel and Giese-Davis pointed out that depression may predict cancer’s progression and mortality through a bidirectional relationship between depression and cancer; depression and cancer can negatively affect each other [7]. Consequently, depression and anxiety among head and neck cancer patients should be adequately treated.

*Experiential avoidance* (EA) has been broadly defined as attempts to avoid thoughts, feelings, memories, physical sensations, and other internal experiences—even when such avoidance causes long-term harm [8]. Currently, negative thoughts, emotions, and sensations are believed not to contribute to psychiatric illnesses; however, a habitual and persistent unwillingness to experience uncomfortable thoughts and feelings (and the associated avoidance and inhibition of these experiences) is thought to be linked to psychiatric illnesses [8, 9]. Additionally, reduced EA also indirectly predicts a higher QoL among cancer patients via its effect on depression symptoms [10]. Therefore, an intervention that successfully reduces EA is predicted to also reduce depression and anxiety symptoms.

#### Posttraumatic growth, hope, and optimism’s influence on quality of life

Despite the negative psychological complications associated with head and neck cancer and its treatment, psychology research has shifted focus in recent years, examining the positive aspects and growth resulting from traumatic experiences of cancer and cancer patients’ QoL. Among the positive psychological experiences which may develop in cancer patients include posttraumatic growth, hope, and optimism. Posttraumatic growth (PTG) describes positive psychological changes experienced as the result of a struggle due to a life-threatening crisis or event. PTG comprises five components, and an individual who has experienced more PTG will better appreciate life and have better interpersonal relationships, more personal strength, higher levels of spiritual development, and/or experience more possibilities in life compared with before development of PTG [11]. PTG results in positive psychological changes beyond pre-trauma levels [11]. It has been shown to be present among head and neck cancer patients [12, 13]. PTG is important and should be emphasized as a positive psychological characteristic among cancer patients because it inversely correlates with depression and psychological distress [14, 15]. It also positively correlates with health-related QoL [15, 16]. However, it should be noted that not all patients with trauma related to living with cancer could trigger the development of PTG. If the traumatic experience of living with cancer is too intense, it may lead to failure for cognitive reprocessing of the traumatic event to search for meaning, which will hamper the development of PTG [17]. Hence, it is pivotal to investigate psychosocial intervention which effectively facilitate the development of PTG.

*Hope* is a positive, goal-directed motivational state and a dispositional trait that enables a tendency to adopt a positive outlook on life [18]. It comprises two components: *agency*, which is the perceived motivation to pursue and achieve goals, and *pathway*, which is the perceived ability to generate approaches to achieving goals [18]. Hope is associated with several positive outcomes for cancer patients. For instance, hope is negatively associated with depression, anxiety, and psychological distress among cancer patients [19–22]. Higher levels of hope are associated with better QoL and spiritual well-being for cancer patients, and it is the most significant factor associated with greater posttraumatic growth among cancer patients compared with other positive psychology elements [23–25].

Similarly, *optimism* is the stable and consistent belief that good things—rather than bad things—will happen in life [26]. Optimism has been shown to positively correlate with psychological well-being and inversely correlate with depression and psychological distress [27]. It is also positively associated with health-related QoL among cancer patients [27–29]. In of head and neck cancer patients’ context, optimism predicts better one-year survival rates independently from confounding demographic and clinical factors [30]. QoL is an important measure and health indicator in the field of psycho-oncology for assessments and treatment outcomes [31]. Since head and neck cancer is associated with a wide range of illness complications and adverse treatment effects that can reduce QoL [32–34], psychosocial interventions that could enhance head and neck cancer patients’ QoL must be investigated.

#### Acceptance and commitment therapy and mindfulness-based stress reduction

We have identified two psychosocial interventions that could enhance cancer’s positive psychological sequelae and reduce its negative psychological sequelae: acceptance and commitment therapy (ACT) and mindfulness-based stress reduction (MBSR). ACT is a third-generation cognitive behavioral approach that uses acceptance and mindfulness processes, as well as commitment and behavioral change processes, to generate psychological flexibility [9]. Psychological flexibility is the ability to act on the long-term chosen values in life and accept undesired thoughts, feelings and short-term impulses stemming from distressing life events. Hence, psychological flexibility allows one to control EA, which may be utilized to cope with distressing life events [35].

ACT is useful for cancer patients because it can help them handle the negative emotions resulting from cancer (such as uncertainty, anxiety, sadness, and anger), rather than avoiding these emotions [36, 37]. A meta-analysis of 25 treatment-control comparison studies with a total sample size of 2,256 cancer patients found that ACT greatly affected psychological distress, particularly reducing depression and anxiety symptoms among cancer patients [38]. ACT also greatly increased QoL and hope among cancer patients [38]. Although that study’s sample size may be too small to fully justify ACT’s significant effect on hope, ACT’s main principles that help cancer patients clarify their values and commit to actions are believed to improve their hope [38]. Moreover, an RCT of 410 colorectal cancer survivors reported that ACT significantly increased PTG at six-month and 12-month periods of a telephone-based health coaching intervention using ACT strategies [39]. However, to date, ACT’s effect on PTG, hope, optimism, acceptance, depression, anxiety, and QoL among head and neck cancer patients has not been investigated.

MBSR is an eight-week, standardized group intervention comprising mindfulness meditation and gentle yoga designed to address stress, pain, and illness [40]. Cancer patients’ participation in MBSR has been shown to have increase in spirituality, PTG, self-compassion, and positive states of mind [41–47]. Studies have emphasized that MBSR increases PTG among participating cancer patients immediately after an eight-week intervention [44, 47, 48]. A meta-analysis of 29 studies with a total of 3,476 cancer survivors evaluated mindfulness-based interventions’ efficacy in facilitating mental well-being, revealing that MBSR significantly reduced depression, anxiety, stress, and fatigue while enhancing PTG, QoL, and mindfulness among cancer patients [49]. Moreover, MBSR has been reported to lower psychological distress and improve total, social, and emotional QoL among head and neck cancer patients [50]. To date, however, MBSR’s effect on cancer patients’ hope has not been investigated. Therefore, an investigation of MBSR’s effects on PTG, hope, optimism, depression, anxiety, and QoL among head and neck cancer patients would be interesting. Moreover, a comparison of MBSR’s efficacy compared to ACT would be valuable.

#### Rationale

Head and neck cancer differs from other cancer types due to various psychosocial issues associated with it [3, 4]. Moreover, the devastating complications of both cancer itself and cancer treatments’ side effects—such as fatigue, pain, speech and swallowing problems, breathing problems, mucositis, xerostomia, and trismus—further disrupt many functions and daily living activities, increasing psychological distress and decreasing QoL [32, 33]. Therefore, an investigation of the psychosocial interventions that could enhance PTG, hope, optimism, and QoL among head and neck cancer patients is crucial. Reducing these patients’ internalized stigma and EA could also ultimately restore these cancer survivors’ mental and physical well-being. ACT and MBSR have been reported to enhance positive psychology and alleviate psychological distress among cancer patients [38, 49]. However, data regarding ACT and MBSR’s effects on positive psychology, psychological sequelae and QoL in head and neck cancer patients are lacking. ACT’s effects on PTG, hope, optimism, QoL, depression, anxiety, and EA among head and neck cancer patients have not been studied. Although MBSR has been reported to lower psychological distress and enhance QoL in head and neck cancer patients, its effects on positive psychology and EA have not been investigated. Hence, MBSR may act as a good comparator intervention to ACT for evaluating its efficacy on positive psychology, psychological sequelae and QoL among head and neck cancer patients. Therefore, we have proposed a three-armed RCT to evaluate these effects over time compared to a control group receiving treatment-as-usual.

### Objectives

#### Primary objectives

Evaluate ACT’s efficacy in enhancing PTG among head and neck cancer patients compared to MBSR and a control (treatment-as-usual) immediately after the eight-week intervention and 24 weeks post-intervention compared to pre-intervention

#### Secondary objectives

Examine ACT’s efficacy in enhancing positive psychology (such as hope and optimism) among head and neck cancer patients compared to MBSR and a control (treatment-as-usual) immediately after the eight-week intervention and 24 weeks post-intervention compared to pre-interventionExamine ACT’s efficacy in reducing EA among head and neck cancer patients compared to MBSR and a control (no treatment-as-usual) immediately after the eight-week intervention and 24 weeks post-intervention compared to pre-interventionExamine ACT’s efficacy in reducing psychological complications (depression and anxiety) among head and neck cancer patients compared to MBSR and a control (treatment-as-usual) immediately after the eight-week intervention and 24 weeks after intervention compared to pre-intervention.Evaluate ACT’s efficacy in enhancing QoL among head and neck cancer patients compared to MBSR and a control (treatment-as-usual) immediately after the eight-week intervention and 24 weeks post-intervention compared to pre-intervention.

## Methods/Design

### Design

The current study will conduct a multicentre, three-armed, parallel-group, double-blind RCT that is expected to run for three years.

### Setting

This study will be conducted in Advanced Medical and Dental Institute (AMDI) at the Universiti Sains Malaysia (USM) and Universiti Kebangsaan Malaysia Medical Centre (UKMMC). AMDI, USM is a tertiary referral center for oncology in Peninsular Malaysia while UKMMC is a tertiary referral center for various illnesses, including oncology cases in Peninsular Malaysia.

### Support and ethics

This study has received approval from the Human Research Ethics Committee of Universiti Sains Malaysia (code: USM/JEPeM/21040321). The study will be conducted in compliance with the *Declaration of Helsinki* (1974) and its amendments, as well as the *Malaysian Good Clinical Practice Guidelines for Clinical Trials*. The institutional review board will be informed of any modification to the study’s protocol (such as its eligibility criteria, study procedures, outcome measures, scheduled interventions, and data analyses) in writing. This manuscript was written without any deviation from the original protocol submitted to the Human Research Ethics Committee of Universiti Sains Malaysia except we added more details to the title in this manuscript to make it more informative. The title of the original manuscript reads “Randomized controlled trial of acceptance and commitment therapy versus mindfulness-based stress reduction in newly diagnosed head and neck cancer patients”, while the title of this manuscript reads “Acceptance and commitment therapy versus mindfulness-based stress reduction for newly diagnosed head and neck cancer patients: A randomized controlled trial assessing efficacy for positive psychology, depression, anxiety, and quality of life”.

The principal investigator will lead the trial center and closely coordinate with the research coordinator and the site coordinator, participate in subject recruitment, and oversee the study’s consent procedures. A trial monitoring committee has been established. This committee is chaired by the principal investigator, and it will meet weekly to manage the study on a day-to-day basis, audit trial conduct, and prepare reports for submission to the Human Research Ethics Committee of Universiti Sains Malaysia. The trial’s data monitoring and auditing will be conducted by the AMDI’s clinical trial coordination unit at the Universiti Sains Malaysia—independently from the trial’s funder.

All participants will be permitted to withdraw from the study at any time without specifying the reason for their withdrawal, and we will not use any of the information collected from participants who choose to withdraw. Prior to their participation in this study, participants will be informed that the results of this study will only be used for research purposes and will not be recorded in patients’ case files. Participants’ personally identifiable information will not be sought or recorded, and participants’ anonymity will be assured. Each participant will be sequentially assigned a research number (e.g., *RCT001*, *RCT002*, etc.). All documents involved in this study’s assessment of research subjects—including participants’ personal information (socio-demographic, substance history, symptomatology, and questionnaire responses)—will be stored in document files and locked in a cabinet whose key is kept by the corresponding author.

Participants may also withdraw from the study if an adverse event occurs. An *adverse event* (AE) is any untoward medical occurrence involving a participant in a trial intervention that does not necessarily causally relate to this treatment. An AE can be any unfavorable or unintended sign, symptom, or disease that is temporarily associated with the use of an investigational intervention, whether related or unrelated to the investigational intervention. Participants will be issued a study card featuring the research team’s contact details and encouraged to maintain close contact by phone and report any AE. If an AE occurs, the event will be reported in the “Adverse Event” section of the study’s case report form (CRF), and a serious adverse event report will be filled out if necessary (S1 Fig). Such reports would include the AE’s name, date of onset and date of recovery, severity, relationship to the studied intervention, measures undertaken regarding the studied intervention, treatment, and outcome (whether resolved or ongoing). All serious AEs will be reported to the Human Research Ethics Committee of Universiti Sains Malaysia. AE-related criteria that would exclude participants from the study are:

The presence of adverse reactions unrelated to the study that cause subjects to feel uncomfortable continuing this studyThe presence of adverse reactions that may be related to the study, such as an unusual illness that started after a studied interventionUnusual changes in participants’ behavior, temperament, routine, suicidal tendency, or psychotic symptoms that began after a studied interventionAny suspected or unexpected adverse events inconsistent with the generally accepted administration of the ACT and MBSR; in general, psychotherapy patients should not exhibit any side effects or health-detrimental effects

If an unexpectedly serious AE is reported in a subject or more in any of the randomized intervention group (ACT or MBSR), an interim analysis will be conducted to investigate this matter. If the findings of this investigation indicate any safety concerns which is related to the intervention administered (ACT or MBSR), the Trial Monitoring Committee will terminate the trial prematurely. Serious AE which are indication for premature termination of trial include suicidal tendency, life-threatening self-harm, and hospitalization related to psychological adverse events arise from the intervention administered.

Only the study’s corresponding author and co-authors are permitted to access the study’s files for data analysis or publication purposes. The findings of this study will be submitted for publication in peer-reviewed academic journals and for presentation at international conferences and symposia. The study’s principal investigator will be listed as the corresponding author, and authorship eligibility will be based on the International Committee of Medical Journal Editors’ recommendations.

All of this study’s investigators declare no financial or other competing interests in conducting this study.

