### Recruitment process

This study will use a consecutive sampling method. The research team will approach head and neck cancer patients registered at the two targeted institutions and explain the study’s objectives and procedures. Patients who are interested in participating in this study will be screened for inclusion and exclusion criteria by a research team member. All eligible patients will be invited to participate in this study. The study’s purposes and procedures will be thoroughly explained (verbal explanation by the research assistant and a copy of the participant information will also be distributed) to prospective participants before they are invited to participate in this study, their anonymity will be assured, and they will be informed of their right to withdraw from the study at any time and the data collected will be discarded. Eligible patients will be given 48 hours to decide on their participation in the study. Then, participants will sign written informed consent to participate in the study before they enroll in the study.

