### Data analysis

All of this study’s data analysis will be conducted using the Statistical Package for Social Sciences, version 26 (SPSS 26; SPSS Inc., Chicago, Illinois, USA). Initially, the baseline sociodemographic and tumor characteristics will be presented by randomized groups (ACT, MBSR, and control groups).

The mean difference in the primary outcome (total PTGI-SF score) for the three randomized groups (ACT, MBSR, and control groups) at each specific time point (pre-intervention [t_0_], post-treatment at 8 weeks [t_1_] and 24 weeks after intervention [t_2_]) will be assessed using one way analysis of variance (ANOVA) followed by false discovery rate adjustment. For the main pool analysis, mixed linear model will be employed for comparing the primary outcome (total PTGI-SF score) between ACT and control groups and between MBSR and control groups across the three time points (t_0_, t_1_ and t_2_), while controlling for stratification factors such as age and gender. The main effects of intervention in the groups and time points will be presented as estimated marginal mean and standard error of mean. The study’s primary analysis will follow the intention-to-treat (ITT) principle. The data analysis for the study’s secondary outcomes (quality of life, hope, optimism, depression, anxiety, and EA) will be conducted similarly to the primary outcomes’ calculation. In addition, 95% confidence interval will also be presented alongside the main effect. Statistical significance will be two-tailed and set to *p* < 0.05.

To handle any missing data, if the missing data represent less than 5% of the study’s total collected data, they will be ignored. If the missing data represent more than 5% but less than 40% of the total collected and are assumed to be randomly missing, then multiple imputation (restricted maximum likelihood estimation) will be performed using Stata 15. However, if the missing data represent more than 40% of the total collected data or are assumed to be missing either not randomly or completely randomly, then only the collected data will be used for the study’s analysis, and the missing data will be explained as a research limitation in any publications of the study’s findings [68].

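### Discarding all data of participants who withdraw contradicts the intention-to-treat primary analysis

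*Protocol article*

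**What the plan says.** Three sections of the protocol article bear on who is analysed.

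- **Support and ethics.** Participants may leave at any time without a reason, and "we will not use any of the information collected from participants who choose to withdraw". The same section adds: "Participants may also withdraw from the study if an adverse event occurs". It then introduces a list with the words "AE-related criteria that would exclude participants from the study are". Most of the listed events arise after an intervention has begun, and one item concerns "adverse events inconsistent with the generally accepted administration of the ACT and MBSR".
- **Recruitment process.** Before consent, patients are told of "their right to withdraw from the study at any time and the data collected will be discarded".
- **Data analysis.** The "primary analysis will follow the intention-to-treat (ITT) principle". The main analysis is a mixed linear model over t0, t1 and t2. If between 5% and 40% of data are missing and assumed randomly missing, "multiple imputation (restricted maximum likelihood estimation) will be performed using Stata 15".

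The Other measures section separately records reasons for missed sessions, dropout and loss to follow-up, and gives disliking the therapy as one example. No section says how the discard rule and the intention-to-treat statement fit together.

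**The concern.** An intention-to-treat analysis keeps each randomised patient in the allocated arm, using whatever data exist. A rule that bars all use of a withdrawer's data takes that patient out after randomisation, for a reason that arises after randomisation. Three things are at stake.

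1. **Comparability.** Withdrawal can follow an adverse event or dislike of the assigned programme, so it can be related to outcome and may be related to arm. The retained groups are then no longer the randomised groups.
2. **Usable data.** A patient who completes t0 and t1 and withdraws before t2 has a valid week-8 score on the primary outcome. The rule throws it away.
3. **The plan's own remedies.** A mixed model and multiple imputation both work from partial records. Here the partial records are gone.

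This is not a detail that a statistical analysis plan could settle. The promise to discard is made to participants at consent, and no later document can analyse data that they were told would not be used.

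**Working it through.** **Inputs from the protocol article.** Participants section: effect size 0.15, alpha 0.05, power 0.8, 93 patients required in three equal groups, 30% drop-out, 120 enrolled. The article does not say how many of the expected drop-outs would be formal withdrawals.

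**1. The plan's own figures.** The required 93 can be reproduced as a repeated-measures group-by-time interaction with 3 groups, 3 time points and f = 0.15, assuming a correlation of 0.5 between time points and sphericity (neither is stated):

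- noncentrality = f² × N × 3 / (1 − 0.5) = 0.0225 × 93 × 6 = 12.555
- degrees of freedom: 4 and (93 − 3) × 2 = 180
- power = 0.81, and 93 is the smallest multiple of three that reaches 0.80

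The enrolled total follows as 93 × 1.3 = 120.9, given as 120.

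**2. How many patients the rule could remove.** If every drop-out were a withdrawal:

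- removed: 0.30 × 120 = 36
- left: 120 − 36 = 84, or 28 per arm if spread evenly
- shortfall against the requirement: 93 − 84 = 9
- power in the model of step 1: noncentrality 0.0225 × 84 × 6 = 11.34 on 4 and 162 degrees of freedom, giving 0.76

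If no drop-out were a formal withdrawal, none would be removed. The retained number falls below 93 once withdrawals exceed 1 − 93/120 = 22.5%. Part of the shortfall comes from inflating by 1.3 rather than dividing by 0.7 (93/0.7 = 132.9). What the discard rule adds is that the 36 contribute nothing, instead of their scores up to withdrawal.

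**3. How far selection could move a mean (assumed figures, no true effect).** Let the outcome Y be standard normal with higher values better, and let the log-odds of withdrawal be a − bY, with a set to give the stated loss. The retained mean is E[Y(1 − p(Y))] / (1 − loss), where p(Y) is the withdrawal probability. By numerical integration:

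| Loss in the arm | b = 0.5 per SD | b = 1.0 per SD |
|---|---|---|
| 20% | 0.096 SD | 0.173 SD |
| 30% | 0.143 SD | 0.253 SD |
| 40% | 0.189 SD | 0.332 SD |

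These are shifts in one arm. The bias in a treatment contrast is the difference between two arms' shifts:

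- equal loss and equal slope: 0
- 30% against 20%: 0.143 − 0.096 = 0.047 SD, and 0.253 − 0.173 = 0.080 SD
- 40% against 20%: 0.189 − 0.096 = 0.093 SD, and 0.332 − 0.173 = 0.159 SD

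A simpler assumption gives a similar order. If withdrawers score D below stayers in every arm, the bias is D times the difference in loss: 0.3 × 0.10 = 0.03 SD up to 0.5 × 0.20 = 0.10 SD.

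In these examples the arm with more withdrawal looks better, because patients doing worse are assumed to leave. The sign reverses if patients doing better leave, or if the control arm loses more.

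**4. The adverse-event list.** Support and ethics orders that data go unused only for those who choose to withdraw. For participants excluded under the adverse-event criteria it says that they leave the study and nothing about their data. Two readings remain open: data kept and analysed, or data dropped. Only the first fits the intention-to-treat statement.

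**The case against.** The strongest reply is that the discard rule is narrow. It covers people who formally choose to withdraw. Patients who miss visits or are lost to follow-up stay in the data and are handled by the mixed model and, under conditions, by imputation. That stands, and it rules out several stronger readings that a reader might infer:

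- **That the trial becomes a completer analysis.** It does not. The set is all randomised patients minus withdrawers.
- **That stopping sessions triggers deletion.** No section says so, and missed sessions are recorded separately. The fair criticism is that leaving the study is not separated from withdrawing consent to data use.
- **That participants excluded for adverse events have their data deleted.** The text does not state this; it is an ambiguity.
- **That the rule favours the therapies.** Neither unequal removal nor its direction is established. Only one adverse-event criterion names ACT and MBSR, the control arm also attends an eight-session programme, and dissatisfied control patients may leave too.
- **That safety information is erased.** Adverse events are entered in the case report form, serious ones go to the ethics committee, and an unexpected serious event in an active arm triggers an interim analysis. At most the final tabulation is at risk.

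A second reply is that the right to withdraw requires the rule. It does not: a participant can be free to leave, and free to ask for deletion, without deletion being automatic.

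None of this reconciles the discard rule with the intention-to-treat statement.

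**Conclusion.** The contradiction is in the text and needs no assumption: the discard rule and the intention-to-treat primary analysis cannot both be carried out. It affects the primary and secondary outcomes alike and should be resolved before the analysis, preferably before further patients consent.

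Its size is conditional. Up to 36 of 120 patients would be removed if all the planned drop-out were withdrawal, leaving 84 against 93 required, with power near 0.76 in the model that reproduces 93. The actual number could be anything from none to that bound. The bias between arms is zero if selection is the same in each arm. Under the assumed scenarios with unequal loss it runs from 0.03 to 0.16 SD, with the direction unknown. The shift of 0.14 to 0.25 SD at 30% loss concerns one arm's mean and should not be read as a treatment contrast.

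The adverse-event exclusions are a separate and lesser matter: the fate of those participants' data is unstated and must be made clear.

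**What to change.** 1. Amend the Support and ethics and Recruitment process sections, and the participant information, so that data collected up to withdrawal are retained and analysed in the allocated arm unless the participant explicitly asks for deletion.
2. Report the number of deletions requested, by arm.
3. Reconcile the adverse-event exclusion wording in Support and ethics with the Data analysis section, so that such an exclusion does not remove data already collected from the intention-to-treat analysis. Clinical management of these participants stays with the investigators.

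The cost is an ethics amendment and a revised information sheet, and participants must be told that data to date are kept by default. Participants already consented under the promise to discard remain covered by it unless they re-consent, so a delay enlarges the group that the amendment cannot reach.
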